## Background

Frailty is a common and clinically significant condition within geriatric populations [1]; the latter predominantly due to its association with adverse health outcomes such as hospitalisation, disability and mortality [1–6]. The exact prevalence of frailty within this population is poorly defined due to the lack of a single standardised operational definition for the classification of frailty. However, it is generally believed that the prevalence of frailty amongst community-dwelling older adults ranges between 7.0 and 16.3% [1, 7]. Presently, there are no well-evidenced, pooled estimates of the prevalence of frailty amongst older adults in care home settings. Although, it could be postulated that this prevalence would likely be higher than that of community-dwelling older adults, given that older adults living in care homes typically tend to be chronologically older, and often exhibit a greater number of comorbidities and a reduced functional capacity. However, these differences routinely become non-significant once standardised for age [8]. Additionally, the estimated prevalence of frailty in nursing homes (where qualified nursing care is required, in addition to care assistance) is approximately 52.3% [9]. As such, the prevalence of frailty in care homes likely lies somewhere in between that of community-dwelling older adults and nursing home residents; given the inherent nature of these respective settings, and the demographics of the individuals who occupy them.

Although there is no one standardised and universally utilised operational definition for the classification of frailty, one of the most commonly utilised is the Fried frailty phenotype [2]. This proposes that frailty be defined as a clinical syndrome in which three or more of the five following criteria are present: unintentional weight loss (≥ 10 lbs in the past year), self-reported exhaustion, weakness (grip strength), slow walking speed and low levels of physical activity.

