##### Follow-up testing

Follow-up testing will be conducted 6 weeks post-intervention cessation for the feasibility and patient-centred outcomes of the study. All data will be gathered within a period of approximately 12 days from all participants.

Adherence rates in the intervention group will be recorded as the number of repetitions completed in a set (90% required for adherence to that exercise), and then the number of exercises for which there was a 90% adherence. If participants meet these parameters for each exercise session, they will be considered to be in 100% adherence to the intervention. For example, if a participant performs 95% of all exercises in one session, then they will be considered to be in adherence for that session. If they then continue this level of adherence for the remaining 41 sessions, they will have a 100% adherence. If a participant adheres to 95% of the intervention for 36 sessions, but only 80% for 6 sessions, then they will have an 86% adherence rate. Ninety percent of all exercises performed within that session will signify adherence to that session. Adherence rates, whether very high or somewhat low may signify that the intervention may have been too demanding, too easy or optimal. Information will also be collected throughout the study related to uptake and retention rates.

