#### Sample size

This study aims to recruit a convenience sample of *n* = ~ 48 participants: 24 intervention and 24 regular care control. No formal power calculations were conducted due to the feasibility nature of this study. This estimated sample size is based on optimistic projections following preliminary discussion with care home residents with relation to potential uptake.

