#### Quantitative analysis

Statistical analysis of the patient-centred outcomes will be performed using IBM SPSS (Statistical Package for Social Sciences) software. These analyses will be performed as part of the limited-efficacy testing regarding the potential impact of the intervention on the patient-centred outcomes (proposed primary dependent variables of the future clinical trial). Specifically, for this research, the type of statistical analysis which will be used will be as follows: 2 × 3-way independent measures ANOVA’s (analysis of variance consisting of a two independent variables; the specialised resistance training intervention, and control group, each with three levels: baseline, post-intervention (6 weeks) and follow-up (12 weeks) will be carried out for all patient-centred outcomes. A subsequent post-hoc test will be utilised if a significant main effect or interactions are found. Pearson product correlations will also be utilised between various socio-demographic variables (such as age and sex) and the patient-centred outcomes of this study to assess possible relationships between differences in these socio-demographic factors and changes in the patient-centred outcomes of the study.

Central tendency and variability measurements consisting of the measurement of parameters such as the mean, median and mode, and standard deviation and range of scores respectively, will also be utilised during the analysis of data for illustrative purpose. Significance levels will be set at 0.05 (*p* ≤ 0.05), and effect sizes will be reported for all analyses. Additionally, in order to establish if the assumptions of parametric statistics have been met in relation to the assumption that there is a normal distribution of data, the data will be analysed for skewness and kurtosis. As the quantitative component of this study has not been powered given the feasibility nature of the study, the examination of the efficacy of the intervention to impact these variables is limited and interpretation treated with caution pending the results from the future powered clinical trial. All results will be reported with 95% confidence intervals.

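### The fixed three-visit ANOVA handles missed visits less well than the collected data allow, and can bias arm differences if loss is outcome-related and differs by arm

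*Protocol article*

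**What the plan says.** The Quantitative analysis section of the protocol article commits to one method for the efficacy outcomes, a "2 × 3-way independent measures ANOVA", with "each with three levels: baseline, post-intervention (6 weeks) and follow-up (12 weeks) will be carried out for all patient-centred outcomes". The software is named ("Statistical analysis of the patient-centred outcomes will be performed using IBM SPSS") but the procedure within it is not. On the threshold it says "Significance levels will be set at 0.05". Effect sizes and 95% confidence intervals are promised.

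The Sample size section plans about 48 "participants: 24 intervention and 24 regular care control", and states that "No formal power calculations were conducted due to the feasibility nature of this study". The article gives no expected dropout rate, no outcome SD and no correlation between visits.

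Three other places bear on missed visits:

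- The Background describes frailty as clinically significant because of "its association with adverse health outcomes such as hospitalisation, disability and mortality".
- Follow-up testing says "Information will also be collected throughout the study related to uptake and retention rates".
- Safety reporting and monitoring lists, among the standard actions after an adverse or serious adverse event, a recommendation to withdraw unless the attending physician clears the participant to go on exercising.

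**The concern.** The same residents are measured three times, and in a frail population some will miss a visit. How such a resident enters the analysis follows from the model chosen, and the article has chosen it. There are two ways to run it.

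- **As worded (independent measures).** Each resident-visit is a separate row. A resident seen at baseline and week 6 but not at week 12 contributes two rows, and the week-12 mean is the mean of those who attended. The model makes no use of the absent resident's earlier values to inform the week-12 comparison.
- **As a repeated-measures ANOVA.** This is the form the design suggests, although the article does not name it. The standard SPSS repeated-measures procedure deletes a resident with any visit missing, so a week-6 result already collected is discarded because the week-12 visit was missed.

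Loss that is related to outcome and differs by arm is plausible here. Only one arm trains, and the withdrawal recommendation is tied to clearance to exercise. If exercise-arm residents who do poorly are the ones who leave, the remaining exercise mean is too favourable. These results are meant to inform the testing times of the future trial (Table 1, limited-efficacy row) and feed the overall feasibility assessment (Qualitative analysis), so a bias favouring exercise would carry forward.

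**Working it through.** There is no figure in the plan to reproduce: the sample size has no effect size, SD, power or dropout behind it. The check concerns the behaviour of the named method.

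**Inputs.** From the article: 24 per arm; visits at baseline, 6 and 12 weeks. Assumed, because the article gives none: SD 1 at each visit; correlation ρ = 0.7 between any two visits; loss after week 6 of 10–30%, with 15–25% as the main range.

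**1. Precision if residents with a missed visit are deleted.** The standard error is multiplied by √(1/(1 − a)), where a is the proportion lost.

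| Loss a | Complete residents per arm | Multiplier |
|---|---|---|
| 15% | 24 × 0.85 = 20.4 | 1.085 |
| 20% | 24 × 0.80 = 19.2 | 1.118 |
| 25% | 24 × 0.75 = 18.0 | 1.155 |

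The interval is therefore about 8–15% wider at 15–25% loss. For the week-6 contrast this cost is avoidable, because those values were collected. At week 12 part of the loss is unavoidable under any method.

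**2. Bias when only the exercise arm's loss depends on the week-6 value.** Control loss is random at the same rate. Let s be the amount by which the mean week-6 value of exercise-arm stayers exceeds that of everyone randomised to the arm. With equal correlations:

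- week-12 arm difference as worded: bias = ρ·s = 0.7s
- listwise week-6 change from baseline: bias = s − ρ·s = 0.3s
- listwise week-12 change from baseline: bias = ρ·s − ρ·s = 0

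Simulation with 1,000,000 residents, loss logistic on the week-6 value:

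| Logistic slope | Loss | s | Week 12 as worded | Week 6 listwise |
|---|---|---|---|---|
| 1 | 15% | 0.13 | +0.09 | +0.04 |
| 1.5 | 15% | 0.18 | +0.12 | +0.05 |
| 1.5 | 24% | 0.27 | +0.19 | +0.08 |
| 3 | 24% | 0.35 | +0.25 | +0.10 |

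The simulated biases agree with 0.7s and 0.3s. An estimate using all observed visits by likelihood was within 0.002 SD of the truth at week 12 in each of these scenarios.

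**3. Other loss mechanisms.** A separate simulation (300,000 per arm, true week-12 effect 0.40 SD, logistic slope 2) gave these estimates of the week-12 change contrast at 10/20/30% loss:

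| Mechanism | As worded | Listwise | Likelihood |
|---|---|---|---|
| Random in both arms | 0.40/0.40/0.40 | 0.40/0.40/0.40 | 0.40/0.40/0.40 |
| Week-6 value, same in both arms | 0.40/0.40/0.40 | 0.40/0.40/0.40 | 0.40/0.40/0.40 |
| Week-6 value, exercise arm only | 0.50/0.58/0.67 | 0.40/0.40/0.40 | 0.40/0.40/0.40 |
| Decline from baseline to week 6, exercise arm only | 0.40/0.40/0.40 | 0.45/0.49/0.53 | 0.40/0.40/0.40 |

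Each ANOVA form is biased under one of the two differential mechanisms and not the other. The likelihood estimate is unbiased in all four, as it should be, because every mechanism here depends only on observed values.

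**The case against.** **Scope.** This is a condensed article. A rule for missing visits, a definition of the analysis set and a tabulation of withdrawals are commonly left to the full protocol or analysis plan. That stands: their absence is no finding. What can be judged is the method the article does fix.

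**Stronger readings.** A reader might infer that the ANOVA has no valid place for a resident who misses a visit, or that ordinary attrition is enough to bias the efficacy results. The documents support neither. As worded, the model keeps every observed visit. Deletion arises only if it is run as a repeated-measures ANOVA, which the article does not name. Attrition alone does not bias the arm contrast: with random loss or the same mechanism in both arms, both forms returned the true value. If both arms lose their worst performers, both show a spurious rise over time, but it cancels between arms.

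**Size and likelihood.** Every magnitude rests on assumed loss, correlation and mechanism. The study is short, takes place where the residents live, has assessment windows of about 12 days, and excludes people who are terminally ill with a life expectancy shorter than follow-up. With 24 per arm and SD 1, the 95% half-width for a simple arm difference is 2.013 × √(2/24) = 0.58 SD, larger than any bias shown here. Efficacy is the secondary aim, unpowered, and the article itself calls for caution in reading it. All of this stands and limits the consequence. But caution about power does not correct a bias in one direction, and a better method costs very little.

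**Overlap.** Calling repeated visits on the same residents independent misstates the error term even with complete data. That is a separate error, and the firmer one in the same sentence.

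**Conclusion.** The concern holds in a conditional form. The named ANOVA uses the collected data less well than a model for repeated measures. As worded, it can bias the week-12 arm difference by about 0.1–0.25 SD. As a listwise repeated-measures ANOVA, it can bias the week-6 change contrast by about 0.04–0.1 SD and widens its interval by about 8–15%. The bias figures assume 15–24% loss after week 6, correlation 0.7, exercise-arm loss driven by the week-6 value and random control loss; the widening assumes 15–25% loss. The article supplies none of these values. Differential loss is plausible from the design and the withdrawal recommendation, but it is not shown to be likely. Without it, the cost is precision only. The change is worth making because it is cheap, not because a confirmatory conclusion is at risk.

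**What to change.** In the Quantitative analysis section, replace the ANOVA with a likelihood-based mixed model for repeated measures (SPSS MIXED): arm, visit and arm by visit as fixed effects, unstructured within-resident covariance, and all observed visits of all randomised residents in their allocated arm. Report the week-6 and week-12 arm differences from this model with 95% confidence intervals. Showing the number of residents observed at each visit by arm beside them would let readers judge whether loss differed.

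The cost is a rewording and slightly more analysis work in the same software. The model assumes missing at random, so it does not protect against loss driven by unobserved decline or by death, and the text should say so. The same change also corrects the separate error of treating visits on the same residents as independent.

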**Discussion:**

The most immediate implication of this research from a scientific perspective is informing the feasibility, and potential efficacy, of a proposed future clinical trial within this setting. Additionally, if the study proves feasible, and the limited-efficacy testing proves positive, this study also has the potential to lead to advancement in the care for frail geriatric populations within residential care settings; and the ability to measurably improve various aspects of health and functional capacity within this population. This study has been granted a favourable ethical opinion by the London Harrow NHS Research Ethics Committee and is sponsored by the University of Birmingham. The findings of this study will be disseminated through publication in open access scientific journals, public engagement events, online via social media, conference presentations and directly to study participants.

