#### Patient-centred outcomes

The patient-centred outcomes of this feasibility study relating to multi-dimensional health (and comprising the proposed primary dependent variables of the future clinical trial) are as follows:

Physiological*: Serum Cortisol, Dehydroepiandrosterone (DHEAS), cortisol: DHEAS ratio, C-reactive proteins (CRP), Interleukin 6 (IL-6), Tumour Necrosis Factor alpha (TNFα), Interferon gamma (IFNy).

Functional: Hand grip strength (Southampton protocol [23]), leg strength and power output [24, 25], Short Physical Performance Battery (SPPB) [26], Katz Index of Independence in Activities of Daily Living (Katz ADL) [27], Fried Frailty Phenotype [2].

Psychological/Emotional: Geriatric Depression Scale (GDS) [28], Hospital Anxiety Depression Scale (HADS) [29], Perceived Stress Scale (PSS) [30].

Cognitive: Standardised Mini-Mental State Examination (SMMSE) [31].

Social: Interpersonal Support Evaluation List (ISEL-12) [32].

*All blood samples will be obtained through the process of phlebotomy (venepuncture). Serum will be analysed for the physiological patient-centred outcomes relating to cortisol and DHEAS (assessed by commercial ELISA kit). C-reactive protein and inflammatory cytokines (IL-6, TNFα, IFNy) will be assayed using a multiplex commercial kit (R&D Systems).

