## Discussion

### Implication of the research

As this is a feasibility study, the most immediate implication from a research prospective is the assessment of the feasibility of the proposed future clinical trial within this setting; which will allow for a more detailed, informative and robust understanding of the influences of the specially adapted resistance training intervention on the primary dependent variables of the future clinical trial (the multi-dimensional health and functional capacity of frail older adults within residential care settings). Additionally, frailty can also have an enormous impact on an individual’s life, in addition to the lives of their loved ones, and even an impact on society as a whole [10]. As such, if the study does prove feasible, and the limited-efficacy testing proves positive, this study also has the potential to have far reaching implications; most importantly leading to the advancement of care for frail geriatric populations within residential care settings and the ability to measurably improve various aspects of their overall health and functional ability, as well as benefitting the lives of their loved ones.

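### The ANOVA plan follows up any significant main effect or interaction and does not single out the between-arm change, so two of its three triggers do not estimate the treatment effect

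*Protocol article*

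**What the plan says.** The Quantitative analysis section of the protocol article specifies "2 × 3-way independent measures ANOVA’s" (arm by visit, with visits at baseline, 6 weeks and 12 weeks), which "will be carried out for all patient-centred outcomes". The level is fixed: "Significance levels will be set at 0.05". The follow-up rule is: "A subsequent post-hoc test will be utilised if a significant main effect or interactions are found". The section presents these analyses as the limited-efficacy testing of the intervention's potential impact. It does not say which of the three effects carries that meaning.

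The outcomes are listed under Patient-centred outcomes. They serve the study's secondary aim (Aims and objectives) and are the intended primary variables of the later trial.

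The same section says that the quantitative part is unpowered, that interpretation must be cautious pending the later trial, and that effect sizes and 95% confidence intervals will be reported.

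The abstract's Discussion attaches implications for care to the case "if the study proves feasible, and the limited-efficacy testing proves positive", and Implication of the research repeats this: "if the study does prove feasible, and the limited-efficacy testing proves positive". Neither place defines a positive result.

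**The concern.** In a randomised design with one pre-randomisation and two later visits, the treatment effect is the difference between arms in change from baseline. The stated rule gives the same trigger to two effects that measure something else.

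- **Time main effect.** This is change common to both arms. Design overview itself names practice effects and maturation as threats, and justifies the control group as the protection against outside influences. A trigger on the time effect does not use that protection.
- **Arm main effect.** This averages all three visits, including the one before randomisation. A real post-baseline effect is diluted, and chance imbalance at baseline enters the contrast.

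The results are meant to be used. Table 1 asks whether 6 weeks is long enough for benefit and says the answer will inform the testing time points of the later trial. The Qualitative analysis section feeds the limited-efficacy results into the final feasibility assessment. A shared time trend, or a baseline imbalance, could be carried forward as evidence about the intervention.

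**Working it through.** The protocol gives no power, effect size, SD, correlation or family-wise error rate, so there is no stated figure to reproduce.

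**Inputs from the protocol**
- 24 per arm, 48 in total (Sample size).
- Three visits; level 0.05 per F-test; three F-tests per outcome (arm, time, interaction).
- Outcomes: 7 blood measures ("Serum Cortisol, Dehydroepiandrosterone (DHEAS), cortisol: DHEAS ratio, C-reactive proteins (CRP), Interleukin 6 (IL-6), Tumour Necrosis Factor alpha (TNFα), Interferon gamma (IFNy"); 5 functional, or 6 if "leg strength and power output" counts as two; 3 psychological, or 4 if the two HADS subscales are scored separately (an assumption); 1 cognitive; 1 social. Total 7 + 5 + 3 + 1 + 1 = 17, up to 7 + 6 + 4 + 1 + 1 = 19.

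**Assumptions, not in the protocol**
- Equal SD of 1 at each visit; equal within-person correlation ρ between visits; no missing data; a mixed ANOVA with the correct error terms.
- Effects of 0.3 SD (common shift) and 0.5 SD (treatment), each present at both later visits.

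**1. Time main effect when both arms shift equally and treatment does nothing**

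Visit means (0, 0.3, 0.3) have mean 0.2 and squared deviations 0.04 + 0.01 + 0.01 = 0.06. The noncentrality is 48 × 0.06/(1 − ρ), with df 2 and 92.

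| ρ | Noncentrality | Probability that p ≤ 0.05 |
|---|---|---|
| 0.5 | 5.76 | 55% |
| 0.7 | 9.60 | 78% |
| 0.8 | 14.40 | 93% |

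These are per outcome.

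**2. Power for a true 0.5 SD treatment effect at ρ = 0.7**

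- *Arm main effect.* Averaged difference: (0 + 0.5 + 0.5)/3 = 0.333, a loss of one third. Variance: 2(1 + 2ρ)/(3 × 24) = 4.8/72 = 0.0667. Noncentrality: 0.111/0.0667 = 1.67, df 1 and 46. Power 24%.
- *Interaction.* Arm differences (0, 0.5, 0.5) have squared deviations from their mean summing to 0.1667. Noncentrality: (24/2) × 0.1667/0.3 = 6.67, df 2 and 92. Power 62%.
- *Baseline-adjusted difference at 6 weeks.* Variance: 2(1 − ρ²)/24 = 2 × 0.51/24 = 0.0425. Noncentrality: 0.25/0.0425 = 5.88, df 1 and 45. Power 66%.

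**3. Chance of at least one significant F-test when nothing is happening**

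Per outcome: 1 − 0.95³ = 14.3%. If all tests are independent:
- all three effects: 1 − 0.95^51 = 92.7% (17 outcomes) and 1 − 0.95^57 = 94.6% (19 outcomes);
- interactions only: 1 − 0.95^17 = 58.2% and 1 − 0.95^19 = 62.3%.

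Many of these outcomes will be correlated; cortisol and DHEAS, for example, also appear as their own ratio. A simulation of the mixed ANOVA (2,000 replicates, 24 per arm, within-person correlation 0.6) gives, for 17 and 19 outcomes:

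| Correlation between outcomes | Any of three effects | Interactions only |
|---|---|---|
| 0.3 | 86% and 88% | 49% and 53% |
| 0.5 | 78% and 81% | 38% and 44% |
| 0.7 | 63% and 66% | 28% and 30% |

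**The case against.** The strongest reply is that the quoted sentence says only when a post-hoc test is run, which is ordinary ANOVA practice. A reader might infer that any one significant F-test would make the limited-efficacy testing positive, so that a positive outcome is almost guaranteed under no effect. The documents do not support that. They never define the word, and they use it in conditional discussion of implications, not as a decision rule. The 93% to 95% figure also needs independent outcomes and counts all three effects.

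A reader might also treat the 17 to 19 outcomes as co-primary. They are not: feasibility is the primary aim here, and these outcomes serve the secondary aim. Formal multiplicity control is not essential in an unpowered feasibility study, and it could sit in an analysis plan that is not shown. Its absence is not part of this point.

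The protocol already promises effect sizes, confidence intervals and cautious interpretation, and its reason for having a control group implies that the between-arm comparison is intended. That stands, but it does not settle the matter. The caution is about lack of power. It does not say which contrast counts, and mistaking a shared trend for benefit is not a power problem.

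Finally, the calculations for the time effect and for power assume a mixed ANOVA, while the text names independent measures. Taken literally, with visits treated as independent, the simulation puts the true size of the arm test near 19% and of the interaction test near 0.1%. The figures above therefore describe the rule under correct error terms. A literal reading would not rescue it.

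**Conclusion.** The point holds as a defect in the stated analysis rule. The protocol fixes a follow-up trigger on three effects for every patient-centred outcome, and only one of the three addresses the treatment effect.

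The probabilities and powers in the working are illustrations. They rest on the assumed shift, effect and correlations, and would move with other values. What does not depend on them is that the time effect contains no between-arm comparison, and that the arm main effect loses one third of an effect that is constant over the two later visits.

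The chance of some significant result under no effect is best given as a range, about 63% to 95% for all three effects and about 28% to 62% for interactions alone. It supports asking for a defined efficacy quantity. It does not show that the study would be declared positive by chance.

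**What to change.** In Quantitative analysis:
- remove main effects as a trigger for follow-up testing;
- state that the efficacy quantity for each outcome is the baseline-adjusted difference between arms at 6 weeks, with the 12-week difference secondary, each with its 95% CI;
- label time and arm main effects as descriptive.

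In the abstract and in Implication of the research, replace the condition that the testing proves positive with a statement that estimates, confidence intervals and SDs will be reported to inform the future trial.

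This changes wording only; no data collection or sample size is affected. The cost is fewer p-values to quote and an efficacy statement that sounds less favourable.
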